### Study management

#### Selection committee

A selection committee composed of investigators from each center will review the medical history and the indications for inclusion in the RADDI protocol.

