### Trial intervention and visit schedule

#### Randomization

Cluster randomization was utilized. The intervention was applied at the facility level to avoid the possibility of experimental contamination at the patient level. Sixteen tertiary hospitals across China have been randomly assigned to the routine and deferred dialysis groups using a random number generator. At each site, on referral to the study, participants will be sequentially allocated a unique identifying number to be used for all subsequent study documentation. This will ensure confidentiality is maintained.

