#### Blinding

Assessors for the primary outcome in the study will be blinded for the duration of the trial. Assessors for the secondary outcomes will not be blinded.

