### Statistical analysis

#### Sample size

In this study, a cluster randomized design is used. The primary endpoint of the study is death rate, which will be determined by survival analysis. According to the IDEAL study, the death rate was 37% during a median follow-up period of 3.59 years [9]. Because we include relatively stable patients the mortality rate may be lower; we assume the death rate will be 30% or less within 3 years. The project selection window for patient enrollment is 30 months. Sood et al. found an adjusted facility-level intraclass correlation coefficient (ICC) of 0.031 in their work [16]. We get 8 clusters per group. Scholars have proposed that a sample size calculated assuming individual randomization can be inflated by a Design Effect (DE) to reach the required level of statistical power under cluster randomization [17]: DE = 1+ (m-1) ρ, where m is the number of individuals per cluster and ρ is the ICC.

If we assume that alpha = 5%, (1-beta) = 80%, patients are assigned 1:1, a difference of 10% in death rates between these two groups is considered acceptable. We use log-rank tests to get the events (87 vs 57) with the Power Analysis and Sample Size Software, version 13 (NCSS, LLC. Kaysville, Utah, USA) and the number of individuals per group is 473. Thus, the number of total events under the consideration of cluster effects is 198 (128 vs 70). This is an endpoint driven study. We will complete the study when we get enough endpoint events, which is 198 events.

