## Discussion

Optimal timing for chronic dialysis initiation in ESKD patients is currently unknown. The transition period from the pre–ESKD phase to the ESKD phase of CKD is critical for patients. In our previous study, we found that mortality rates in the first 2 months were highest for new chronic dialysis starters (41.9 and 16.6 per 100 patient-years) [18]. Determining optimal timing for dialysis initiation is of great importance. This study protocol represents a large, randomized study evaluating the efficacy and safety of deferred and routine dialysis intervention for an advanced CKD Chinese population. The IDEAL study demonstrated no significant difference in survival between treatment groups. However, the average GFR were 12.0 ml/min/1.73m^2^ in the early start group and 9.8 ml/min/1.73m^2^ in the late start group, which were relatively higher than those recommended in recently released guidelines. In China, because of limited medical resources, dialysis is routinely started for ESKD patients at a much lower eGFR. In our study, the reference eGFR for initiating dialysis is 7 ml/min/1.73m^2^ or lower. No interventional study has targeted such a low reference eGFR to date. This study will improve our understanding of the timing of chronic dialysis.

Our study is a cluster randomized trial. As pointed out, designing interventions targeting delayed dialysis initiation at the facility level might be difficult in the United States, because dialysis facilities do not usually participate in the decision to initiate dialysis [4]. In China, nephrologists in large hospitals make the decision to dialyze ESKD patients and then provide treatment in their affiliated dialysis facilities. Thus, this enables us to design our research to be carried out at the facility level. Since we follow CKD patients from earlier CKD stages, the lead-time and survivor bias can also be eliminated. Randomized trials are the gold standard method to measure the effects on outcomes [19]. Thus, this design can enable us to overcome inherent shortcomings in observational studies such as selection bias and confounding factors.

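### The article says its design overcomes selection bias and confounding, but patients are recruited openly after only 16 hospitals were assigned, and the limitations do not mention this

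*Protocol article*

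**What the plan says.** **Order of events.** The Randomization section reports the hospital allocation as already done: "Sixteen tertiary hospitals across China have been randomly assigned to the routine and deferred dialysis groups using a random number generator." Patients come afterwards: "At each site, on referral to the study, participants will be sequentially allocated a unique identifying number". Enrolment is spread over time: "The project selection window for patient enrollment is 30 months." The Sample size section gives the number of units: "We get 8 clusters per group." No stratification, matching or other restriction is described.

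**Who decides on inclusion.** Under Pre-inclusion visit, patients are asked for individual consent and each proposed inclusion is validated by the responsible researchers. Under Selection committee: "A selection committee composed of investigators from each center will review the medical history and the indications for inclusion in the RADDI protocol."

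**Who knows the arm.** Under Intervention, the researchers apply the arm's own eGFR threshold for starting dialysis. The Blinding section covers one group only: "Assessors for the primary outcome in the study will be blinded for the duration of the trial." Secondary-outcome assessors are said to be unblinded, and nothing is said of recruiters or the committee.

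**What is claimed.** The Discussion says "this design can enable us to overcome inherent shortcomings in observational studies such as selection bias and confounding factors". The Abstract states the avoidance of both problems as an aim. The Discussion then lists five limitations: generalisability, behaviour under observation, contamination, financially motivated delay, and suboptimal care. Neither recruitment after allocation nor the small number of randomised units is among them.

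**Analysis.** The Analysis section names Cox regression for the clinical events and a cluster-design equivalence test of proportions. It names no covariates.

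**The concern.** Randomising hospitals protects the comparison of hospitals. It does not by itself protect the comparison of patients when they are identified and consented after the hospital's arm is known. Several entry criteria need judgement, such as stable CKD, short life expectancy and uncontrolled malignancy. Patients, too, can accept or decline knowing their hospital's policy. If the arms differ in who is approached or who agrees, that difference goes directly into the comparison of deaths and cerebro-cardiovascular events.

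Separately, eight units per arm leave room for sizeable imbalance by chance, even with perfectly neutral recruitment. A reader of the Discussion would conclude that both problems have been dealt with by design.

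**Working it through.** **1. Passages side by side.** Hospitals are assigned first (Randomization). Patients are then referred, consented and validated (Randomization, Pre-inclusion visit, Selection committee). The researchers run the arm-specific threshold (Intervention), and blinding is confined to primary-outcome assessors (Blinding). That recruiters know the arm is therefore a firm inference, not a statement in the text. The Discussion's claim carries no qualification for this sequence.

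**2. The plan's own figure.** The hazard ratio implied by 30% vs 20% deaths is ln(0.8)/ln(0.7) = 0.626. With two-sided alpha 5% and 80% power, the Schoenfeld formula gives 4 × (1.960 + 0.842)² / (ln 0.626)² = 143 events, and the Freedman formula gives 148. The article states 87 + 57 = 144, so this step reproduces. Below, 473 patients per group is taken as stated.

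**3. Chance imbalance in a baseline factor.**
- From the article: 473 patients and 8 hospitals per arm, so m = 473/8 = 59.1; DE = 1 + (m − 1) × ICC.
- Assumed: prevalence p = 0.30; equal hospital sizes; normal approximation; the factor's ICC, varied from 0.01 to 0.10. The middle value borrows the article's "adjusted facility-level intraclass correlation coefficient (ICC) of 0.031", which it does not tie to any baseline factor.
- SD of the arm difference = √[2 × p(1 − p) × DE / 473]. With DE = 1 this is √(2 × 0.21/473) = 0.0298. With ICC 0.031 it is √(2 × 0.21 × 2.80/473) = 0.0499.

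| ICC of the factor | DE | SD of difference (points) | Chance of a gap of at least 5 points |
|---|---|---|---|
| individual randomisation | 1.00 | 3.0 | 9% |
| 0.01 | 1.58 | 3.7 | 18% |
| 0.031 | 2.80 | 5.0 | 32% |
| 0.10 | 6.81 | 7.8 | 52% |

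For a factor that belongs to the hospital itself, the arm difference has SD √(2/8) = 0.5 between-hospital SDs, and exceeds 0.5 SD in about 32% of allocations.

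**4. What a case-mix gap does to the endpoint.** This is a separate illustration, with no true treatment effect. Take the article's 30% death rate in the reference arm. Assume 40% of its patients are high-risk, with a risk ratio of 2 or 3.
- Risk ratio 2: low-risk rate 0.30/(0.6 + 0.4 × 2) = 0.214, high-risk rate 0.429. A high-risk share of 35% in the other arm gives 0.65 × 0.214 + 0.35 × 0.429 = 0.289, and HR = ln(1 − 0.289)/ln(0.7) = 0.96.
- Risk ratio 3, same 5-point gap: death rate 0.283, HR 0.93.
- A 20-point gap: HR 0.83 (risk ratio 2) or 0.75 (risk ratio 3).

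The gap could favour either arm; the article gives no basis for a direction or a size.

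**The case against.** **The claim is only relative.** The Discussion sentence compares the design with observational studies, and the Abstract states an aim. That is fair, and randomising hospitals does remove one important source of confounding. But neither sentence is qualified, and the limitations list, where a qualification would belong, is silent.

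**The committee may be a safeguard.** The text does not say that members know the arm or rule on their own hospital's patients, and investigators from all centres may form a cross-centre panel. This stands. The point therefore rests mainly on the order of events, the Blinding section and the Discussion claim. A panel would in any case not reach bias at referral and consent.

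**Randomisation may have been restricted.** An unrestricted draw over 16 hospitals gives an 8/8 split in only 12,870/65,536 = 20% of cases, so some restriction is likely. It cannot be said that allocation was simple, only that no stratification or matching is described.

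**A reader might infer that the outcome model is unadjusted.** The article does not say so. It names no covariates, and a condensed article commonly leaves these to the full protocol or SAP, so that silence is no error.

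**A reader might also infer that adjustment would buy a known gain in power.** The documents do not support this. The 0.031 is already described as an adjusted ICC, the article does not say for which outcome or covariates, and it gives no lower value to move to.

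**Conclusion.** The concern holds as an overstated property of the design. With open recruitment after allocation and eight hospitals per arm, selection bias and imbalance in case mix remain possible, and the article should not say that the design overcomes them.

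The size of any recruitment bias cannot be derived from the documents. Chance imbalance can only be illustrated: roughly 18% to 52% of allocations show a gap of at least 5 points in a 30%-prevalence factor over an ICC range of 0.01 to 0.10, against 9% under individual randomisation. Prevalence and ICC are assumptions. Under the assumed risk structure, a 5-point gap in one factor shifts the hazard ratio only to 0.93–0.96, well short of the design value of 0.626. Only larger gaps shift it materially.

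This does not show that the Cox analysis is wrong. It shows that stating a prespecified adjustment is worthwhile in this design.

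**What to change.** 1. **Wording.** Qualify the Discussion claim and the Abstract aim: randomising hospitals removes confounding in the choice of arm on average, but recruitment after allocation and eight hospitals per arm leave room for differences in case mix. Add both points to the limitations. Cost: a few sentences, in the next protocol version or the results report.
2. **Analysis.** State that the Cox comparison of the primary endpoint allows for clustering by hospital and is adjusted for a short prespecified set of baseline factors: age, inclusion eGFR, serum albumin, and prior cardio- or cerebrovascular disease if the medical history captures it. Keep the unadjusted result as supportive. eGFR and albumin are scheduled at the inclusion visit in Table 4, and age is needed for the eGFR formula. Cost: a paragraph, or a pointer if the SAP already does this. Two drawbacks should be stated: the adjusted hazard ratio is conditional, and adjustment covers measured factors only, so it would not by itself justify the Discussion claim.
3. **Reporting.** Present screening and baseline data by arm and by hospital, so that readers can judge differential recruitment. Cost: additional tables, and screening counts if sites keep them.
4. **Masking.** For any patients still to be enrolled, give the existing selection committee dossiers with site and arm removed. Cost: minor administrative work. This does not reach bias at referral and consent, and the article does not show whether enrolment is still open.

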#### Monitoring

A contract research organization (CRO) has been hired for this study. The coordinator will ensure that the study is conducted in accordance with the International Council for Harmonization of Technical Requirements for Pharmaceuticals for Human Use (ICH) standards of good clinical practice (GCP) through site monitoring visits. The CRO provides an online website to enter data that includes range checks for data values. The website can also act as a reminder for the investigator to follow up with patients. The monitoring plan has been written and agreed to. The data-monitoring committee has been established to monitor 100% of the data.

### Safety

#### Adverse events

Any adverse events (AE) occurring during the course of this study must be recorded in the corresponding case report form (CRF). In addition, the participants will be asked questions about the occurrence of AE during the researchers’ examination of vital signs and blood collection. “Clinical adverse events” refers to a disease, signs or symptoms that occur during the course of the study. All the clinical AE, whether or not they are considered to be relevant to the study, will be documented and described on the AE page of the CRF by the investigator. The names of the disease or disorder will be recorded (i.e. diagnosis). The researchers will provide the participants with the results of the laboratory tests that are considered clinically significant and will be recorded on the AE page of CRF. All clinically significant abnormal laboratory results, whether related to this study, will be reported. Abnormal laboratory results that are considered serious will be reported promptly and the patient will be treated appropriately. For all adverse events, the researchers are required to follow up with the patient until the events are eliminated or stabilized and to record the outcomes of the events.

## Discussion

Optimal timing for chronic dialysis initiation in ESKD patients is currently unknown. The transition period from the pre–ESKD phase to the ESKD phase of CKD is critical for patients. In our previous study, we found that mortality rates in the first 2 months were highest for new chronic dialysis starters (41.9 and 16.6 per 100 patient-years) [18]. Determining optimal timing for dialysis initiation is of great importance. This study protocol represents a large, randomized study evaluating the efficacy and safety of deferred and routine dialysis intervention for an advanced CKD Chinese population. The IDEAL study demonstrated no significant difference in survival between treatment groups. However, the average GFR were 12.0 ml/min/1.73m^2^ in the early start group and 9.8 ml/min/1.73m^2^ in the late start group, which were relatively higher than those recommended in recently released guidelines. In China, because of limited medical resources, dialysis is routinely started for ESKD patients at a much lower eGFR. In our study, the reference eGFR for initiating dialysis is 7 ml/min/1.73m^2^ or lower. No interventional study has targeted such a low reference eGFR to date. This study will improve our understanding of the timing of chronic dialysis.

Our study is a cluster randomized trial. As pointed out, designing interventions targeting delayed dialysis initiation at the facility level might be difficult in the United States, because dialysis facilities do not usually participate in the decision to initiate dialysis [4]. In China, nephrologists in large hospitals make the decision to dialyze ESKD patients and then provide treatment in their affiliated dialysis facilities. Thus, this enables us to design our research to be carried out at the facility level. Since we follow CKD patients from earlier CKD stages, the lead-time and survivor bias can also be eliminated. Randomized trials are the gold standard method to measure the effects on outcomes [19]. Thus, this design can enable us to overcome inherent shortcomings in observational studies such as selection bias and confounding factors.

Recently, the Canadian Kidney Knowledge Translation and Generation Network published its study protocol “Knowledge Translation Interventions to Improve the Timing of Dialysis Initiation: Protocol for a Cluster Randomized Trial,” which aimed to evaluate the efficacy and safety of a knowledge translation intervention to promote the intent-to-defer approach in clinical practice [20]. The study designs have some similar components. However, they are very different. The emphasis of the Canadian research is to determine whether active knowledge translation intervention can reduce early dialysis starts. However, our study aims at evaluating the efficacy and safety of early and late dialysis initiation and the influence of timing on subsequent clinical outcomes directly.

An endpoint event-based power estimation is adopted in this study. It will allow all sites to finish together and avoid trial power being affected by alterations in accrual times. It will also protect the study power from lower than predicted event rates.

We acknowledge the following study limitations: (1) The results of the randomized study have limited generalizability due to the healthier nature of patients who participate in trials; (2) There may be a tendency for patients enrolled in clinical trials to alter their behavior due to awareness of being observed [19]. Thus, all patients may have relatively better outcomes; (3) Although this is facility-level research aimed at avoiding experimental contamination, the facilities in the routine group may also adopt the strategies in the delayed group unintentionally; (4) Patients in the routine group may actively delay their dialysis due to poor financial conditions. Thus, the eGFR rates may be similar at the end of the study and may endanger the power of this study; and (5) Patients with financial problems (e.g. without medical insurance) in both groups may get suboptimal medical care, which may impact their outcomes.

Even if the eGFR values of patients in both groups at dialysis initiation are low and not sufficiently different, this study will still potentially have economic, health, and scientific implications. Completing this study will add new knowledge about the timing of dialysis initiation.

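### Closing at 198 events does not by itself protect power when 16 hospitals are randomised: at the plan's ICC, power at that total depends on the number and evenness of hospitals, and more events cannot bring it to 80%

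*Protocol article*

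**What the plan says.** The Randomization section makes the hospital the unit of allocation: "Sixteen tertiary hospitals across China have been randomly assigned to the routine and deferred dialysis groups using a random number generator". The Sample size section puts 8 clusters in each group, cites a study that "found an adjusted facility-level intraclass correlation coefficient (ICC) of 0.031 in their work", and inflates by "DE = 1+ (m-1) ρ, where m is the number of individuals per cluster and ρ is the ICC". It gives 144 events (87 vs 57) and 473 patients per group, then 198 events (128 vs 70) after allowing for clustering. The study ends when 198 events have occurred, and no condition is attached about which hospitals supplied them.

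The Discussion then claims two benefits for event-based estimation. The first is "It will allow all sites to finish together and avoid trial power being affected by alterations in accrual times". The second is that power is safe if events occur less often than predicted. The limitations listed there include one about power (similar eGFR in the two groups), but none about the number of hospitals or uneven recruitment.

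**The concern.** In an individually randomised trial with a time-to-event endpoint, the event total largely fixes the information, so accrual can slip without loss of power. When hospitals are randomised, the variance of the treatment effect also has a between-hospital part. More events do not reduce that part, and it grows when hospitals contribute unequally. The plan's own design effect shows the dependence, since it contains the number of patients per hospital. It also assumes that this number is the same everywhere.

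A sponsor who relies on the Discussion would close at 198 events believing power to be secured, or would simply wait longer if in doubt. A null result could then be read as coming from an adequately powered trial.

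**Working it through.** **Inputs (Sample size section).** "If we assume that alpha = 5%, (1-beta) = 80%, patients are assigned 1:1"; "we assume the death rate will be 30% or less within 3 years"; "a difference of 10% in death rates between these two groups is considered acceptable"; "The project selection window for patient enrollment is 30 months"; 8 hospitals per group; ICC 0.031. I read the effect as 30% vs 20%, so HR = ln 0.7 / ln 0.8 = 1.598 (or 0.626) and log HR = 0.469. Sidedness is not stated; two-sided 5% reproduces the base figure.

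**The plan's figure before clustering.** Schoenfeld: 4 × (1.960 + 0.842)² / 0.469² = 143 events, against the stated 144. With 2.5 years of accrual in 3 years overall (assumed) and exponential survival, event probabilities are 18.5% and 12.1%. Then 473 per group gives 87 vs 57. So 144 and 473 reproduce, and 473 carries no cluster inflation.

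**The cluster step.** m = 473/8 = 59.1, so DE = 1 + 58.1 × 0.031 = 2.80, and 144 × 2.80 = 403. The stated ratio 198/144 = 1.375 would need m of about 13. The figure 198 therefore does not reproduce. That is a separate error.

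**Power at 198 events.** Effective events = 198/DE. Power is Φ(0.469 × √(effective events)/2 − 1.960), or the noncentral t equivalent for a hospital-level test on 14 df. For unequal sizes, DE = 1 + ((1 + CV²)m − 1)ρ. The documents give no size CV; the values below are assumptions to show the range.

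| Hospitals | DE | Effective events | Power, t (14 df) | Power, normal |
|---|---|---|---|---|
| Equal | 2.80 | 71 | 45% | 50% |
| Size CV 0.65 | 3.58 | 55 | 37% | 41% |
| Size CV 1.0 | 4.63 | 43 | 30% | 33% |

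Losing hospitals acts in the same way. With 946 patients and 198 events, 7 equal hospitals per group give 41% (t) or 47% (normal), and 6 give 37% or 43%. Under individual randomisation 198 events would give 91%.

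**Low event rates.** If rates are lower, 198 events take more patients. With the ICC held at 0.031, power at 198 events is 64% (t) or 71% (normal) from 396 patients (DE 1.74), 54% or 60% from 660, and 45% or 50% from 946. If instead the between-hospital CV of the event rate is held constant, this movement disappears.

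**Ceiling.** Effective patients needed per group for 80%: (1.960 + 0.842)² × (0.3 × 0.7 + 0.2 × 0.8) / 0.1² = 290. As m grows, effective patients per group tend to 8/0.031 = 258. At 258, SE = √(0.37/258) = 0.0379 and 0.1/0.0379 = 2.64. Power is then Φ(2.64 − 1.96) = 75%, or 69% on 14 df. A beta-distributed simulation of hospital risks gave 68.8%. Equivalently, 290 × 0.031 = 9.0 clusters per group is more than 8.

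**Cross-check on the log-rate scale** (between-hospital CV of the rate about 0.35, from the ICC at 25% risk, or separate values for the two groups). Equal hospitals give 47-48% (t) or 52-53% (normal) at 198 events, 56-57% or 62-63% at 403, and 68-70% or 74-76% with unlimited events.

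**Sensitivity to the ICC** (t / normal). The ceiling is 86% / 91% at 0.02 and 58% / 64% at 0.04. Power at 198 events with equal hospitals is 55% / 61% and 39% / 44%.

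**The case against.** The quoted sentence speaks of accrual times, beside a remark about sites finishing together. Read narrowly, it is right: if recruitment only runs late and the same hospitals supply the same shares, power at 198 events does not change. That stands, and it is why the point is limited to changes in hospital number, shares or size.

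Most of the fall from 80% occurs with equal hospitals and belongs to the inflation error. On the plan's formula, with m held at 59, 403 events would be worth 144 independent ones. The drop to 45-50% must not be charged twice. What belongs here is the further fall with uneven hospitals, and the fact that extra events do not close the gap.

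The ceiling is conditional. The article does not say which outcome the ICC of 0.031 describes, and an ICC of 0.02 would lift the ceiling above 80%. The 128 vs 70 split on 473 per group (27.1% vs 14.8%) would imply a ceiling of about 90% on 14 df, but that effect conflicts with the stated 10-point difference. A reader might infer that power is stuck near 70% whatever is assumed. The documents do not support that.

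A reader might also infer that nothing controls uneven recruitment. The article cannot show this: it cites a full protocol, version 4.0, and a written monitoring plan, neither of which is shown, and site targets commonly sit in such documents.

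**Conclusion.** The assurance in the Discussion is wrong as a general statement for this design and contradicts the design effect in the Sample size section. Under 30% vs 20%, two-sided 5%, 8 hospitals per group and an ICC of 0.031 taken to apply to this endpoint, 198 events do not fix power. It is about 45-50% with equal hospitals and about 30-41% across the two assumed size CVs. No event count reaches 80% under these inputs. The dependence on the number and evenness of hospitals holds for any positive ICC; the level of the ceiling does not, because it turns on the ICC, the effect size and the test. It would go too far to say that any change in accrual costs power, or that uneven recruitment accounts for the whole shortfall.

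**What to change.** 1. In the Discussion, replace the two claimed protections with a statement that power is limited by the 16 hospitals and falls with uneven recruitment, and that event-based closure guards only against calendar delay with hospital numbers and shares unchanged.
2. In the Sample size section, use DE = 1 + ((1 + CV²)m − 1)ρ and restate the power over a range of ICCs (for example 0.02 to 0.04). Correct the step from 144 to 198 at the same time, as a separate matter.
3. At closure, quote power from the observed hospital sizes and events per hospital, pooled and blinded to arm, not from the event total alone.

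No per-hospital target or recruitment ceiling is proposed. A target of 59 would be the uninflated 473/8, and a ceiling is a trade-off that would not lift the limit set by 16 hospitals.

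The cost is wording, one formula, a recalculation and a short tabulation at closure. The downside is that the quoted power becomes less favourable.
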